**Table 1. Study procedures**

|  | **Before inclusion** | **On admission**  **-** Treatment phase | **Follow-up** | *(months)* |  |
| --- | --- | --- | --- | --- | --- |
|  |  |  | 3 | 6 | 12 |
| **Standard screening, baseline procedures** | **x** |  |  |  |  |
| **Check eligibility (inclusion criteria)** | **x** |  |  |  |  |
| **Patient Information** | **x** |  |  |  |  |
| **Obtain written informed consent** | **x** |  |  |  |  |
| **Randomisation** |  | **x** |  |  |  |
| **Photography** |  | **x** *- During surgery* |  |  |  |
| **Biopsies** |  | **x** *- During surgery* |  |  |  |
| **Re-epithalisatie 95% (days)** |  | **x** |  |  |  |
| **Complications** |  | **x** *- Per-operatively and post-operatively* |  |  |  |
| **Cutometry** |  |  | **x** |  | **x** |
| **Dermaspectrometry** |  |  | **x** |  | **x** |
| **Questionnaires**  - POSAS  - Anchor questions |  |  | **x x** | **x x** | **x x** |
| **Biopsy assessment** |  |  |  |  | **x** |

## Withdrawal of individual subjects

Subjects can leave the study at any time for any reason if they wish to do so without any consequences. The investigator can decide to withdraw a subject from the study for urgent medical reasons.

### Specific criteria for withdrawal (if applicable)

Not applicable

## Replacement of individual subjects after withdrawal

There will be no replacement of individual subjects after withdrawal.

## Follow-up of subjects withdrawn from treatment

Subjects withdrawn from the study will receive every treatment as usual and all the follow ups and after care as foreseen for every other burn patient.

## Premature termination of the study

No criteria are foreseen for premature termination of the study.

# SAFETY REPORTING

## Temporary halt for reasons of subject safety

In accordance to section 10, subsection 4, of the WMO, the sponsor will suspend the study if there is sufficient ground that continuation of the study will jeopardise subject health or safety. The sponsor will notify the accredited METC without undue delay of a temporary halt including the reason for such an action. The study will be suspended pending a further positive decision by the accredited METC. The investigator will take care that all subjects are kept informed.

## AEs, SAEs and SUSARs

### Adverse events (AEs)

Adverse events are defined as any undesirable experience occurring to a subject during the study, whether or not considered related to surgery using hydrosurgery (Versajet) or conventional tangential excision. All adverse events reported spontaneously by the subject or observed by the investiga­tor or his staff will be recorded.

### Serious adverse events (SAEs)

A serious adverse event is any untoward medical occurrence or effect that

- results in death;
- is life threatening (at the time of the event);
- requires hospitalisation or prolongation of existing inpatients’ hospitalisation;
- results in persistent or significant disability or incapacity;
- is a congenital anomaly or birth defect; or
- any other important medical event that did not result in any of the outcomes listed above due to medical or surgical intervention but could have been based upon appropriate judgement by the investigator.

An elective hospital admission will not be considered as a serious adverse event.

The sponsor will report the SAEs through the web portal *ToetsingOnline* to the accredited METC that approved the protocol, within 7 days of first knowledge for SAEs that result in death or are life threatening followed by a period of maximum of 8 days to complete the initial preliminary report. All other SAEs will be reported within a period of maximum 15 days after the sponsor has first knowledge of the serious adverse events.

### Suspected unexpected serious adverse reactions (SUSARs)

Adverse reactions are all untoward and unintended responses to an investigational product related to any dose administered.

Unexpected adverse reactions are SUSARs if the following three conditions are met:

1. the event must be serious (see chapter 9.2.2);
2. there must be a certain degree of probability that the event is a harmful and an undesirable reaction to the medicinal product under investigation, regardless of the administered dose;
3. the adverse reaction must be unexpected, that is to say, the nature and severity of the adverse reaction are not in agreement with the product information as recorded in:

- Summary of Product Characteristics (SPC) for an authorised medicinal product;
- Investigator’s Brochure for an unauthorised medicinal product.

The sponsor will report expedited the following SUSARs through the web portal *ToetsingOnline* to the METC

- SUSARs that have arisen in the clinical trial that was assessed by the METC;
- SUSARs that have arisen in other clinical trials of the same sponsor and with the same medicinal product, and that could have consequences for the safety of the subjects involved in the clinical trial that was assessed by the METC.

The remaining SUSARs are recorded in an overview list (line-listing) that will be submitted once every half year to the METC. This line-listing provides an overview of all SUSARs from the study medicine, accompanied by a brief report highlighting the main points of concern.

The expedited reporting of SUSARs through the web portal Eudravigilance or ToetsingOnline is sufficient as notification to the competent authority.

The sponsor will report expedited all SUSARs to the competent authorities in other Member States, according to the requirements of the Member States.

The expedited reporting will occur not later than 15 days after the sponsor has first knowledge of the adverse reactions. For fatal or life threatening cases the term will be maximal 7 days for a preliminary report with another 8 days for completion of the report.

## Annual safety report

In addition to the expedited reporting of SUSARs, the sponsor will submit, once a year throughout the clinical trial, a safety report to the accredited METC, competent authority, and competent authorities of the concerned Member States.

This safety report consists of:

- a list of all suspected (unexpected or expected) serious adverse reactions, along with an aggregated summary table of all reported serious adverse reactions, ordered by organ system, per study;
- a report concerning the safety of the subjects, consisting of a complete safety analysis and an evaluation of the balance between the efficacy and the harmfulness of the medicine under investigation.

## Follow-up of adverse events

All AEs will be followed until they have abated, or until a stable situation has been reached. Depending on the event, follow up may require additional tests or medical procedures as indicated, and/or referral to the general physician or a medical specialist.

SAEs need to be reported till end of study within the Netherlands, as defined in the protocol

## Data Safety Monitoring Board (DSMB) / Safety Committee

Not applicable

# STATISTICAL ANALYSIS

Data analysis will be performed using SPSS PASW Statistics 23.0 (IBM, New York City). Normality of continuous data will be tested with the Shapiro-Wilk and Kolmogorov-Smirnov test and by inspecting frequency distributions histograms.

## Primary study parameter(s)

Scar quality 12 months post-surgery assessed by the observer score of the POSAS scale will be tested for normality before univariate analyses will be performed. If the data are normally distributed, a paired student’s t-test will be used for comparison of the data. Otherwise the Wilcoxon signed-rank test will be applied.

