## Sample size calculation

Power calculation is based on the result obtained by Scholten et al.^3^ in their retrospective study on scar quality after hydrosurgery versus guarded knife excision.

The mean POSAS Observer Score in the hydrosurgery was 14.7 versus 16.7 in the guarded knife group 12 months post-surgery, with a pooled SD of 6.53, resulting in an effect size of 0.3. Because of the within-subject design, a correction for correlated samples was included, assuming a correlation of 0.4 between POSAS Observer Score within one patient. Given a power of 0.8 and a level of significance of 0.05 a number of 105 patients is needed. Because our primary outcome is not assessed until one year post-surgery we anticipate on a drop out of 30%, which means we will include 137 patients.

Annually approximately 750 patients are admitted to one of the three Dutch burn centres. From these patients approximately 300 will require a surgical intervention of which 240 consists of tangential excision. We expect that the majority of these patients, but at least 144 patients (60%), will be eligible for this study. From these eligible patients we expect 108 patients (75%) to give informed consent to participate in the study per year. So, we expect to be able to include 137 patients in 16 months.

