# INVESTIGATIONAL PRODUCT

## Name and description of investigational product(s)

**The Versajet™ II hydrosurgery system (Smith and Nephew. St. Petersburg, FL, USA)** was CE marked in 2011 and was launched in 2012^7^. It uses a high-pressure jet of sterile normal saline to debride wounds. It is attached to a console, which is then operated by a foot pedal. Physiological saline is forced out of a narrow nozzle. This jet of pressurised normal saline functions like a knife and the hand piece allows debridement and aspiration of debris to occur simultaneously. Pressure can be adjusted to facilitate the desired depth of debridement^7^.

Figure 1. The Versajet™ hydrosurgery system

[
[figure not shown]
](http://www.google.nl/url?sa=i&rct=j&q=&esrc=s&source=images&cd=&cad=rja&uact=8&ved=0ahUKEwjq1OPZnf_OAhWODBoKHX5LBNoQjRwIBw&url=http://aghaii.persianblog.ir/post/51/&psig=AFQjCNHD-mFalGjg-_jtoC1VC6bsRxy5eQ&ust=1473405568021263) [
[figure not shown]
](https://www.google.nl/url?sa=i&rct=j&q=&esrc=s&source=images&cd=&cad=rja&uact=8&ved=0ahUKEwjXzaSDr__OAhUHfRoKHYXAACIQjRwIBw&url=https://www.youtube.com/watch?v=Tq7l6fDF4qw&psig=AFQjCNH7zFKKefknUWQ6-JYbcTDVhcIQlg&ust=1473410231718655)

**Tangential blade excision** relies on the stepwise excision of a layer of tissue using a flat blade, which used to be unguarded. The addition of a guard prevents the removal of excessive amounts of tissue, and most of these knives allow adjustment of the width of the gap between the blade and the guard. If the gap is too narrow, the instrument will glide off the burn without any debridement taking place. Tangential blade excision allows the excision of slithers of tissue until healthy tissue is reached^20^.

During surgery two **punch biopsies** will be taken at both intervention areas pre- and post-excision, using a 3 mm punch, in order to confirm depth of burn. The biopsies will be processed according to a standard protocol. The biopsy will be formalin fixed and processed into 5-μm histological slides. Sections will then be stained with haematoxylin and eosin (H&E). Wound depth, dermal preservation and debridement efficacy will be measured by digital imaging analysis per biopsy.

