# METHODS

## Study parameters/endpoints

### Main study parameter/endpoint

- Scar quality assessed as the total observer score of the POSAS at 12 months post-surgery scored by 2 blinded observers independently^24,25,25^

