### Other study parameters (if applicable)

- Demographics: age, sex
- Burn characteristics: % total burned body surface area (TBSA), anatomical affected site(s), date of injury, burn depth determined by an experienced burn physician and burn depth determined by a LDI-scan on date 2-5 post burn (prior to the operation), date of surgery.
- Clinical characteristics: Fitzpatrick skin type, timing to surgery, wound healing time (measured in days till 95% re-epithelization), determination of bacterial load, comorbidity, weck knife, dermatome and Versajet settings, expansion of skin graft , adverse events (blood loss, graft loss, wound infection) and need for reconstructive surgery.

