## Study procedures

**Peroperatively**

After receiving adequate information and when informed consent is signed two study areas of equal burn deapth are marked as area A and area B (figure 2). This must be documented by photography prior to surgery. We will take a 3 mm punch biopsy from part A and part B (figure A, dot A and B). After the biopsies we randomly allocate part A and B to hydrosurgical- or conventional excision. After-debridement we will take one more punch biopsy from both wound areas (figure 2, dot C and D), adjacent to the previous punch biopsy site in an area of confluent depth, prior to application of a split thickness skin graft. Type of mesh graft and expansion will be standardized to ensure an equal mesh cover of the two intervention areas.

Figure 2. Location of punch biopsies.

[figure not shown]

In this trial we use the smallest punch biopsy with a diameter of 3 mm, as interference is limited since a better scar quality is the aim of this study. Wound tissue is collected before and after excision in both intervention areas, which leads us to the total number of 4 punch biopsies per patient.

The stained biopsy specimens will be analysed using light microscopy. To determine the amount of dermal preservation and hence precision of debridement, the amount of viable tissue on pre- and post-debridement specimens will be recorded.

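### The primary paired test is valid but leaves unused the wound depth measured in each area before allocation; adjusting for it could gain precision at almost no cost.

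*Protocol*

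**What the plan says.** The primary endpoint (Protocol 8.1.1) is "Scar quality assessed as the total observer score of the POSAS at 12 months post-surgery scored by 2 blinded observers independently". For its analysis, section 10.1 states that scar quality at 12 months "assessed by the observer score of the POSAS scale will be tested for normality before univariate analyses will be performed", and that "a paired student’s t-test will be used for comparison of the data" if the data are normal. "Otherwise the Wilcoxon signed-rank test will be applied" No covariate is named in either branch.

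Depth enters the protocol in four other places:

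- Section 8.3 requires that "two study areas of equal burn deapth are marked as area A and area B". A 3 mm punch biopsy is then taken from each area, and only after that are A and B randomly allocated.
- Section 6.1 gives confirming the depth of the burn as the purpose of the biopsies and says: "Wound depth, dermal preservation and debridement efficacy will be measured by digital imaging analysis per biopsy".
- Section 8.1.3 lists depth as judged by a burn physician and "burn depth determined by a LDI-scan on date 2-5 post burn (prior to the operation"). It does not say that either is recorded separately for A and B.
- Table 1 schedules the biopsy assessment at month 12.

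**The concern.** Pairing within a patient removes whatever the two areas share: age, skin type, comorbidity, general healing. It cannot remove a difference between the areas. The areas are marked before the biopsies are taken, so the histological depth cannot have guided the matching. Any remaining A-B depth difference that predicts the scar score stays in the variance of the paired difference.

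The trial measures this quantity in each area before allocation, so treatment cannot affect it and it is a legitimate baseline covariate. The assumed effect is small (0.3 SD), so precision in the primary comparison is worth having. What is at stake is a modest gain in power from data already collected. Adjustment is convincing only if it is fixed before outcomes are seen.

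**Working it through.** **Inputs from Protocol 4.4.** "The mean POSAS Observer Score in the hydrosurgery was 14.7 versus 16.7 in the guarded knife group 12 months post-surgery", so the difference is 2.0. The pooled SD is 6.53 and the effect size 2.0/6.53 = 0.306, which the protocol rounds to d = 0.3. The within-patient correlation is r = 0.4, power 0.80 and alpha 0.05. Sidedness is not stated; two-sided reproduces the plan's figure.

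**Step 1: the plan's own figure.** For an unadjusted paired comparison, in normal approximation:

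n = [(1.960 + 0.842) × √(2(1 − r)) / d]² = 7.849 × 1.2 / 0.09 = 104.65, so 105.

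This matches the protocol. The sample size was therefore set for the unadjusted test. The SD of the paired difference behind it, 6.53 × √1.2 = 7.15, already includes every source of A-B variation, residual depth differences among them.

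**Step 2: power of the unadjusted test.** The standardised paired effect is dz = 0.3/√1.2 = 0.2739. The exact paired t-test with 105 pairs has 79.4% power. The small gap to 80% is the normal approximation in Step 1.

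**Step 3: power of the adjusted test.** Regress the score difference on the depth difference and test the intercept. Two things change:

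- The residual variance is multiplied by (1 − rho²), where rho is the correlation between the depth difference and the score difference.
- The intercept's variance is inflated by about 1 + 1/(n − 3), because the depth difference is uncentred and its sample mean varies around zero. With n = 105 this is 1 + 1/102 = 1.0098. One further degree of freedom is lost.

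So dz(adj) = 0.2739 / √[(1 − rho²) × 1.0098], referred to the noncentral t with 103 degrees of freedom.

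**Assumption.** The documents do not give rho, so a range is shown.

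| rho | (1 − rho²) × 1.0098 | dz(adj) | Power, 105 pairs |
| --- | --- | --- | --- |
| unadjusted | – | 0.2739 | 79.4% |
| 0 | 1.010 | 0.2725 | 79.0% |
| 0.1 | 1.000 | 0.2739 | 79.4% |
| 0.2 | 0.969 | 0.2781 | 80.6% |
| 0.3 | 0.919 | 0.2857 | 82.6% |
| 0.4 | 0.848 | 0.2974 | 85.5% |

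**Step 4: break-even.** Adjustment helps once (1 − rho²) × 1.0098 falls below 1, that is once rho² exceeds about 1/103, or rho about 0.1. Below that it costs at most about 0.4 points of power (79.4% to 79.0%).

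**Step 5: check by simulation.** With 105 pairs and 100,000 runs per setting, the adjusted test's power was 78.8%, 79.6%, 80.6%, 82.7% and 85.6% at rho 0, 0.1, 0.2, 0.3 and 0.4. Type I error was 4.9% to 5.1% throughout.

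**The case against.** The strongest reply is that nothing here is wrong. A paired t-test is a standard, valid test for an intra-patient randomised design, and the trial is sized for it. That stands. A reader might infer that leaving depth out costs the trial power or tilts the comparison. The documents support neither. The 105 reproduces for the unadjusted test, so nothing is lost against plan. Because allocation is random, a chance depth imbalance is ordinary sampling error, which the 5% level covers.

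The benefit may also be small, and this stands too. The areas are chosen for equal depth, and entry is limited to deep dermal burns with full-thickness burns excluded, so there may be little depth difference left to explain. One 3 mm punch per area samples about 0.07 cm² (π × 0.15²) of a burn of at least 50 cm², which makes it a noisy measure. A rho below 0.1 is possible, and there adjustment gains nothing. It would likewise go too far to say that depth is matched by clinical judgement alone: section 8.3 does not say how equality is judged, and section 8.1.3 lists both a physician's assessment and an LDI scan.

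A reader might also credit adjustment with repairing the shortfall after dropout, since 137 × 0.70 leaves about 96 patients. That shortfall comes from inflating as 105 × 1.30 = 136.5 and is a separate matter.

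Finally, adjusted analyses often sit in an SAP, and none is shown here. But section 10.1 itself fixes the primary test as unadjusted, so this is where a change to the primary analysis belongs.

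**Conclusion.** The point holds as a recommendation on efficiency. The primary analysis is valid and adequately described, but it makes no use of a baseline measurement that is taken in each area before allocation and could sharpen the comparison.

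With 105 pairs, d = 0.3, r = 0.4 and two-sided 0.05, adjustment changes power by about −0.4 points at rho 0, nothing at 0.1, and +1.2, +3.2 and +6.1 points at 0.2, 0.3 and 0.4. These figures rest on an assumed rho, a linear relation between depth and score, and depth available for all patients; missing depths would shrink the gain. Because rho is unknown, no single figure can be claimed. The case for acting is that the possible loss is very small and the possible gain is several times larger.

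**What to change.** In section 10.1, prespecify the primary analysis as a linear regression of the within-patient difference in 12-month observer POSAS (hydrosurgery minus conventional) on the within-patient difference in pre-excision biopsy wound depth, coded in the same direction, and test the intercept.

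- **Leave the depth difference uncentred.** The intercept is then the technique effect at equal depth. Centring at the sample mean would return the unadjusted mean difference and undo the adjustment.
- **Use pre-excision tissue only.** Post-excision tissue is affected by treatment.
- **Set a missing depth difference to zero**, so that no patient is lost. Do not substitute the LDI result: the protocol does not say that it is recorded per area, and it gives no common scale with histological depth.
- **Keep the unadjusted paired t-test as a sensitivity analysis**, with the Wilcoxon signed-rank test if the differences are clearly non-normal. This gives the present fallback a defined place.

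The cost is a short rewording of 10.1, one covariate, one degree of freedom and up to about 0.4 points of power if depth proves uninformative. The pre-excision biopsies must be read before the primary analysis, which fits the month-12 assessment in Table 1. No additional patients or measurements are needed.

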**Post-surgery and follow-up**

Patients will be assessed in both the acute phase and during the outpatient follow-up. We will record all complications during and post-surgery and the time to wound closure (95% re-epithelization). Blinded follow-up measurements will be performed at 3, 6 and 12 months post-surgery by trained research nurses and/or junior researchers. These study follow-up visits will take place in the outpatient clinic and the timing is similar to the standard follow up schedule after a burn injury in Dutch specialized burn care.

During this visit the POSAS, anchor questions (global perceived effect) of the POSAS, the Cutometer® and DermaSpectrometer® measurements will be administered and whether the patient has had reconstructive surgery. All study wounds and scars will be documented by photography before excision and 3,6 and 12 months after excision.

*Subjective scar assessment*

Patient and Observer Scar Assessment Score (POSAS)

The Patient and Observer Scar Assessment Scale (POSAS) will be used to assess the scar quality of part A and part B. This validated questionnaire enables both patient and observers to assess the same scar on six different scar characteristics, with roughly an overlap of four characteristics. The patient assesses the scar on pain, pruritus, colour, thickness, surface roughness and pliability, while the observer assesses the scar on vascularity, pigmentation, thickness, relief, pliability surface study areas A and B. Both use a numerically 10-point scale in which 1 represents a scar comparable with ‘normal skin’ while 10 represents the ‘worst scar imaginable’. Both patient and observer independently assess the same scar. The observer assessment will be performed by an experienced and trained observer, either a physician, nurse or researcher. ^23,29^

Anchor question of the POSAS

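### The primary test uses only the 12-month score, so the 30% expected to be lost add nothing, although blinded 3- and 6-month scores could give a modest gain

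*Protocol*

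**What the plan says.** - **Endpoint (8.1.1).** The main parameter is the total observer POSAS at 12 months, scored by two blinded observers.
- **Primary test (10.1).** For normally distributed data, "a paired student’s t-test will be used for comparison of the data"; otherwise the Wilcoxon signed-rank test. Section 10.1 gives the earlier POSAS scores no role.
- **Expected loss (4.4).** "we anticipate on a drop out of 30%, which means we will include 137 patients". The flow chart in section 3 shows loss to follow-up before each of the three visits, and section 8.5 rules out replacement.
- **Earlier scores (8.3).** "Blinded follow-up measurements will be performed at 3, 6 and 12 months post-surgery by trained research nurses and/or junior researchers". Table 1 lists the POSAS at all three visits, and 8.3 applies it to both areas.
- **Other uses of the POSAS.** POSAS scores are secondary endpoints (8.1.2), and the 3-to-6-month change feeds the minimal important change (10.2).

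**The concern.** A paired test on one visit works only with patients who have both areas scored at that visit. The protocol expects nearly a third to be missing then, and it has already arranged to measure the same scale, blinded, on the same two areas at two earlier visits. A patient seen at 6 months but not at 12 carries information on the 12-month difference that the stated test cannot use.

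Two things are at stake. One is some power. The other is the assumption behind the estimate: the completers' mean difference is unbiased only if loss is unrelated to the within-patient treatment difference. A likelihood-based model over the three visits needs only that loss be ignorable given the scores already observed (missing at random).

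**Working it through.** **Inputs from section 4.4.** Means of 14.7 (hydrosurgery) and 16.7 (guarded knife); "with a pooled SD of 6.53, resulting in an effect size of 0.3"; an assumed correlation of 0.4 between a patient's two areas; "Given a power of 0.8 and a level of significance of 0.05 a number of 105 patients is needed"; 30% dropout; 137 enrolled. The sidedness of alpha is not stated.

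**1. The plan's own figure.** The standardised within-patient effect is dz = 0.3/√(2 × (1 − 0.4)) = 0.3/√1.2 = 0.2739. Then n = ((1.960 + 0.842)/0.2739)² = 104.65, so 105. The stated number reproduces with a two-sided test. One-sided gives 83 and does not. The noncentral t gives 107.

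**2. Pairs left at 12 months.** 137 × 0.7 = 95.9, about 96, so 41 are lost. Power of the paired test with 96 pairs is 0.757 by noncentral t (0.765 by the normal approximation).

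**3. Where the shortfall comes from.** 105 × 1.3 = 136.5, so 137; but 105/0.7 = 150. With 150 enrolled, the same paired test keeps 150 × 0.7 = 105 pairs and power of about 0.80 (0.801 normal, 0.794 noncentral t). The fall to about 76% therefore comes from the inflation, not from the choice of test.

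**4. What the 6-month score adds with 137 enrolled.** Let ρ be the correlation between the 6- and 12-month within-patient differences (assumed; the protocol gives none). Let m be the share of patients with a 6-month score who have no 12-month score. The effective number of pairs is n_eff = 96/(1 − m ρ²).

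| Lost patients with a 6-month score | m | ρ | n_eff | Power (noncentral t) |
|---|---|---|---|---|
| none | 0 | any | 96 | 0.757 |
| half | 20.5/116.5 = 0.176 | 0.5 | 100.4 | 0.776 |
| all | 41/137 = 0.299 | 0.5 | 103.8 | 0.789 |
| half | 0.176 | 0.7 | 105.1 | 0.794 |
| all | 0.299 | 0.7 | 112.5 | 0.821 |

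The gain is 0.776 − 0.757 = 0.019 to 0.821 − 0.757 = 0.064, that is, about 2 to 6 percentage points.

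**5. Cross-check with all three visits.** Take adjacent-visit correlations of 0.3 to 0.9, with the 3-to-12-month correlation equal to their square (assumed), and normal-approximation power against 0.765 for completers:
- all losses after month 6: 0.776 to 0.869;
- 10% lost in each of the three intervals: 0.770 to 0.835;
- 15% lost before month 3 and 15% between months 3 and 6: 0.765 to 0.814.

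At a correlation of 0.7 the three patterns give 0.827, 0.800 and 0.782. If every loss came before month 3, the gain would be zero.

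**6. Bias in completers, by simulation.** The SD of the difference is 6.53 × √1.2 = 7.15; the true difference is −2.0; 30% are lost; ρ is 0.5 to 0.7 (assumed).
- Loss depends on overall severity unrelated to the difference: the completer estimate is about −2.0, so there is no bias.
- Loss depends on the signed 6-month treatment difference, odds ratio 1.5 to 2.0 per SD: the completer estimate is −2.42 to −2.96. An analysis that uses the 6-month data returns about −2.0.
- Return depends on the size of the difference in either direction (log-odds slope 0.3 to 1.0 per SD): the bias is about 0 with no treatment effect, and 0.06 to 0.26 points at a true effect of −2.

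**The case against.** The paired test is valid, simple and matched to the sample-size calculation. Enrolling 150 would restore its power without any model. The Summary offers visits by the research team to patients who cannot attend, and section 8.3 aligns study visits with routine follow-up; both should limit loss. A statistical analysis plan, not available here, could add imputation or sensitivity analyses. All of this stands, and it limits the point to a modest improvement. It does not remove it: the 30% is the protocol's own expectation in a plan that already includes those measures, section 10.1 itself names a single-visit test as primary, and enrolling more patients does not change the assumption about who is lost.

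Three stronger readings are tempting, and the document does not support them.
- **That the choice of test costs the trial its 80% power.** Step 3 shows that the inflation does.
- **That attrition bias is large or likely.** Each patient carries both treatments, so a dropout removes both areas together and loss cannot unbalance the arms. A shift that is sizeable against the planned 2 points needs return to depend on which technique did better. The protocol gives no reason to expect this. Section 8.2 keeps the follow-up assessor unaware of the technique and sends the allocation to the local principal investigator and the trial co-ordinator.
- **That the earlier scores are thrown away.** They are unused only in the primary comparison.

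**Conclusion.** The point holds as a worthwhile, low-cost improvement to a method the protocol states. It is not a flaw that invalidates the primary analysis. With 137 enrolled and 30% lost, using the 3- and 6-month scores is worth about 2 to 6 points of power if half to all of those lost have a 6-month score and ρ is 0.5 to 0.7. Other assumed correlations and timings of loss give from nothing to about 10 points. The protocol gives neither the between-visit correlation nor the timing of loss, so no single figure can be claimed. The second benefit is validity under missing at random given earlier scores, which guards against a conditional risk and not a demonstrated bias. The inflation of 105 to 137 should be dealt with as a separate matter.

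**What to change.** In section 10.1, make the primary analysis a linear mixed model for the observer total of each area at 3, 6 and 12 months. Treatment, visit and treatment-by-visit are fixed effects, with a within-patient covariance across areas and visits. Report the 12-month treatment contrast with its 95% confidence interval.

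An equivalent form models the within-patient difference with visit as the only fixed effect and an unstructured covariance. That difference must be hydrosurgery minus conventional. Areas A and B are labels to which treatment is randomised (8.2), so area A minus area B averages to about zero whatever the treatment does.

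Keep the 12-month paired t-test, or the Wilcoxon test if the data are not normal, in completers as a sensitivity analysis.

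The cost is analysis wording only: the visits and scores are already scheduled, and the MIXED procedure in SPSS, the package named in section 10, can fit the model. The price is reliance on missing at random and a slightly more complex model.
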